## Abstract

**Simple Summary:**

Colorectal cancer, a major cause of morbidity and mortality, often requires chemotherapy, which can lead to debilitating side effects such as chemotherapy-induced peripheral neuropathy (CIPN). This study aims to evaluate the benefits of a strength exercise program in reducing CIPN in colorectal cancer patients undergoing chemotherapy. Conducted as a double-blind randomized controlled trial with 44 participants, the study divides them into an intervention group (supervised resistance training and home exercises) and a control group (home exercises only). Primary outcomes will be assessed using the EORTC QLQ-CIPN20 questionnaire, while secondary outcomes include quality of life, body mass index, oxygen consumption, anxiety and depression, fatigue, sleep quality, and various blood parameters. The findings will offer valuable insights into how tailored exercise protocols can improve the quality of life, physical capacity, and treatment outcomes for colorectal cancer patients, advocating for the integration of physical exercise into standard cancer care.

**Abstract:**

**Background:** Colorectal cancer is a leading cause of morbidity and mortality worldwide, with chemotherapy being a crucial treatment despite its significant side effects, such as chemotherapy-induced peripheral neuropathy (CIPN). Physical exercise has shown potential benefits in mitigating these side effects and improving patients’ overall well-being. **Objective:** This study aims to evaluate the efficacy of a strength exercise program in reducing CIPN in patients with colorectal cancer undergoing chemotherapy, along with secondary objectives including impacts on quality of life, body mass index, oxygen consumption, anxiety and depression, fatigue, sleep quality, and various analytical parameters. **Methods:** A double-blind randomized controlled trial was conducted with 44 participants, divided into an intervention group (supervised resistance training twice a week and home exercises) and a control group (home exercises only). The primary outcome measure was CIPN, assessed using the EORTC QLQ-CIPN20 questionnaire. Secondary outcomes included assessments using the EORTC QLQ-C30, the 6-minute walk test, HADS, FACT-F, and MISS, along with various blood parameters. **Results and Conclusions:** The study will provide insights into the effectiveness of physical exercise in managing CIPN and improving various health parameters in colorectal cancer patients. By developing tailored exercise protocols, this research aims to enhance patient quality of life, optimize treatment outcomes, and reduce the incidence of debilitating side effects, thereby supporting the integration of physical exercise into standard oncological care.

## 1. Introduction

Colon cancer is one of the leading causes of morbidity and mortality worldwide, with an increasing incidence in many developed countries. In Spain, it is one of the most common types of cancer, accounting for approximately 15% of all cancer cases diagnosed, with an incidence of around 41,000 new cases annually [1]. The mortality associated with colon cancer is significant, although there have been notable improvements in five-year survival rates, which currently stand at around 65%, thanks to advances in treatments and early diagnosis [2]. Early diagnosis is crucial and has been facilitated by screening programs such as colonoscopy and fecal occult blood tests, which allow the detection of precancerous lesions and early-stage cancer. Treatments for colon cancer include surgery, radiotherapy, immunotherapy, and notably, chemotherapy [3]. Chemotherapy is especially relevant in adjuvant treatment to reduce the risk of postoperative recurrence and in metastatic disease to control tumor growth and prolong survival. Modern chemotherapeutic agents, combined with targeted and supportive therapies, have significantly improved treatment outcomes, providing patients with better recovery prospects and an enhanced quality of life during and after treatment.

Chemotherapy is a crucial treatment in the fight against colon cancer, but unfortunately, its impact is not limited solely to cancer cells. Chemotherapeutic agents, designed to target rapidly growing cells, also affect healthy tissues, leading to various side effects. One of the most common adverse effects is peripheral neuropathy, a condition that affects the peripheral nerves and can manifest as sensations of tingling, numbness, pain, or weakness in the limbs [4].

Chemotherapy-induced peripheral neuropathy can be especially challenging for patients with colon cancer, as it further worsens the quality of life during an already difficult period. The nerves responsible for motor and sensory function are compromised, affecting the patient’s ability to perform daily activities and weakening their physical endurance. This phenomenon adds to the emotional and physical burden of battling cancer [5].

However, there are tools that can positively influence these adverse effects, such as physical exercise. Although it may seem contradictory, regular physical exercise has been shown to have beneficial effects on peripheral neuropathy. Physical exercise can improve blood circulation and promote the regeneration of damaged peripheral nerves. Additionally, exercise helps alleviate the pain and discomfort associated with neuropathy, thereby strengthening patients’ functional capacity [6].

Scientific research has demonstrated that physical exercise has multiple benefits for cancer patients, beyond alleviating peripheral neuropathy. Various studies have indicated that regular physical activity can significantly improve immune function, which is crucial for patients undergoing treatments that weaken the immune system. Exercise helps increase the production and efficiency of immune cells, enhancing the body’s ability to fight infections and potentially inhibiting the growth of cancer cells [4].

Furthermore, physical exercise has been associated with a reduction in cancer-related fatigue, one of the most debilitating symptoms experienced by patients during and after treatment. Fatigue can severely limit patients’ ability to engage in daily activities and reduce their quality of life. Research has shown that structured exercise programs, including aerobic and resistance activities, can diminish the sensation of fatigue and improve energy levels and mood, allowing patients to lead more active and fulfilling lives [7].

Physical activity also plays a vital role in weight management and body composition, important factors for cancer survival and recovery. Obesity and overweight are associated with poorer prognosis in many types of cancer, including colon cancer [8]. Regular exercise helps maintain a healthy weight, reduce body fat, and improve muscle mass, which not only contributes to a better quality of life but can also reduce the risk of cancer recurrence and improve overall treatment outcomes. Scientific evidence strongly supports the inclusion of physical exercise as an integral part of the treatment plan for cancer patients [9].

It is essential to highlight that any exercise plan should be tailored to the individual capabilities of each patient, and medical supervision is crucial. Therefore, the combination of chemotherapy and carefully planned physical exercise offers a comprehensive strategy to address both the disease and its side effects, providing colon cancer patients with a better quality of life during their recovery journey.

It is of vital importance to conduct research on the implementation of physical exercise programs in patients with colon cancer to control all the previously mentioned symptoms, such as peripheral neuropathy, fatigue, decreased immune function, and weight management. These investigations should focus on developing personalized and safe exercise protocols that can be effectively integrated into standard oncological treatment [10]. By generating robust evidence on the benefits and best practices for including physical exercise in the management of colon cancer, patient quality of life can be significantly improved, treatment outcomes optimized, and the incidence of debilitating side effects reduced [11]. Moreover, these studies can provide crucial data to guide healthcare professionals in prescribing specific exercise programs, ensuring that patients receive evidence-based interventions that maximize their physical and emotional well-being throughout the recovery process [12].

Therefore, we set the following study objectives. As the main objective, we aim to evaluate the efficacy of a strength exercise program in chemotherapy-induced neuropathy in patients with colorectal cancer undergoing chemotherapy treatment. And as secondary objectives, the following:To assess the impact of a strength exercise program on quality of life in patients with colorectal cancer undergoing chemotherapy treatment.To evaluate the impact of a strength exercise program on body mass index in patients with colorectal cancer undergoing chemotherapy treatment.To evaluate the impact of a strength exercise program on maximum oxygen consumption in patients with colorectal cancer undergoing chemotherapy treatment.To evaluate the impact of a strength exercise program on anxiety and depression in patients with colorectal cancer undergoing chemotherapy treatment.To evaluate the impact of a strength exercise program on fatigue in patients with colorectal cancer undergoing chemotherapy treatment.To evaluate the impact of a strength exercise program on sleep quality in patients with colorectal cancer undergoing chemotherapy treatment.To evaluate the impact of a strength exercise program on analytical parameters (Hb, inflammatory markers, renal function, etc.) in patients with colorectal cancer undergoing chemotherapy treatment.

## 2. Materials and Methods

### 2.1. Study Design and Setting

A double-blind randomized controlled trial was conducted at the Faculty of Nursing and Physiotherapy, University of Salamanca (Spain), following the Consolidated Standards of Reporting Trials (CONSORT) Statement [13]. The current treatment protocol is described according to the recommendations of SPIRIT [14]. The protocol for this trial received approval from the Ethics Committee of the University of Salamanca (record number 1209) and was conducted in accordance with the Declaration of Helsinki. The clinical trial was registered in ClinicalTrials.gov (registration number NCT06404359) (Supplementary File S2, Study flow chart).

### 2.2. Participants and Eligibility Criteria

Participants diagnosed with colorectal cancer undergoing adjuvant chemotherapy treatment were recruited from the outpatient clinics of the Day Oncology Hospital at the University Assistance Complex of Salamanca and from the Asociación Española Contra el Cáncer (AECC).

The inclusion criteria were as follows:Individuals diagnosed with colorectal cancer undergoing chemotherapy treatment.Sedentary individuals who have not engaged in physical activity in the last 8 weeks.Ability to understand assessment tests and perform exercises.

The exclusion criteria:Listing contraindications for engaging in physical exercise: Severe musculoskeletal diseases, severe cardiovascular disease, bone metastases, and other conditions as determined by a healthcare professional.Patients who need to stop treatment early due to intolerance to treatment.

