### 2.4. Outcomes

In the initial assessment, all variables, including sociodemographic factors, will be measured. Subsequently, all outcome variables will be assessed at the end of the 8-week intervention.

Personal and sociodemographic variables are as follows:Age (years)Sex (male or female)Weight (kilograms), height (meters) and body mass index (kg/m^2^)Time since diagnosis (years and months)Stage of the disease.Tumor location (colon or rectum).Type of chemotherapy and number of cycles.Radiotherapy (yes/no).

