#### 2.4.1. Primary Outcomes

The primary outcome measures are chemotherapy-induced peripheral neuropathy (CIPN). Self-reported neuropathy was evaluated using the European Organisation for the Research and Treatment of Cancer Quality of Life (EORTC QLQ) CIPN20 questionnaire, comprising 20 items categorized into three subscales that assess sensory, motor, and autonomic symptoms. Each item was rated on a Likert scale from 1 ‘not at all’ to 4 ‘very much’. Scores were then converted to a 0–100 scale, with higher scores indicating greater symptom severity.

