
### 2.5. Sample Size

The sample size calculation was performed using statistical software (G*Power 3.1). The calculation was carried out for a two-independent-group t-test. The effect size (d = 1.11) was estimated from the mean difference on the Chemotherapy-Induced Peripheral Neuropathy (CIPN) Trial Outcome Index (TOI) scale, obtained from Zimmer et al., 2017 [24], due to the similarity of interventions, and from the study by Balnd et al., 2019 [24], where the same scale (EORTC QLQ-CIPN 20) was used in the same group of patients but with a different intervention. A significance level of 0.05 and power of 95% were established. The estimated sample size was 38 subjects. Taking into account a 20% dropout rate based on the previous study [24], the required number of subjects was 44, with 22 subjects in each group.

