### 2.6. Allocation and Randomization

To conduct the randomization process in a clinical trial, Microsoft Excel 2020 was used to generate a list of random numbers assigned to the participants. Each participant was given a unique number from the list. Those assigned an odd number were placed in the experimental group, while those assigned an even number were placed in the control group. This method ensures a random and equitable distribution of participants across both groups, minimizing bias and ensuring the validity of the clinical trial results.

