### 2.8. Statistical Methods

For the descriptive analysis of the data, normality will be checked with the Kolmogorov–Smirnov and Shapiro–Wilk tests (*n* < 30). Normally distributed variables will be defined by the mean, standard deviation, and value interval, while variables that do not follow a normal distribution will be defined by median and interquartile range. The qualitative variables of the study will be defined by frequencies and percentages.

Regarding quantitative analysis, a correlation analysis (Pearson’s correlation coefficient) will be used to demonstrate the validity of the assessment procedure selected in our study. Cronbach’s alpha coefficient will be used to demonstrate its reliability. For the comparison of two means, Student’s *t*-statistic inferential analysis (parametric test for independent samples), the Mann–Whitney U-statistic (non-parametric tests with two independent samples), and Wilcoxon’s *t*-test (non-parametric tests for repeated means) will be used. The comparison of three or more means has also been used and will be analyzed by means of an ANOVA test in the situation of independent groups (parametric via Snedecor’s F -ANOVA- and non-parametric via Kruskal–Wallis’ H). For repeated measures, Snedecor’s F test will be used in the parametric way and Friedman’s test in the non-parametric way. Correlations will be carried out by two methods: Pearson’s correlation (normal distribution) or Spearman’s correlation (non-normal distribution). Multivariate logistic regression analysis will be performed to determine the variables associated with events of interest. In the logistic regression model, variables that have been significant in the bivariate analysis or that are relevant to the study will be introduced into the logistic regression model. For qualitative or categorical variables, contingency tables and the Chi-Square test of significance will be used when there are two independent samples.

*p*-values of less than 0.05 will be considered significant, i.e., with a confidence interval of 95%. The statistical software IBM SPSS Statistics version 28.0.1 will be used.

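### Eligibility leaves neurotoxic exposure open and the named between-group tests are unadjusted, so variation in regimen, cycles and baseline CIPN20 stays in the error term although all three are recorded

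*Protocol article*

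**What the plan says.** Section 2.2 of the protocol article lists three inclusion criteria. The one about chemotherapy reads "Individuals diagnosed with colorectal cancer undergoing chemotherapy treatment". No agent, planned exposure, cycle at entry or baseline neuropathy status is required. The paragraph above the list is somewhat narrower: "Participants diagnosed with colorectal cancer undergoing adjuvant chemotherapy treatment were recruited". The only exclusion that concerns chemotherapy is "Patients who need to stop treatment early due to intolerance to treatment", which is neither a neurotoxicity nor a timing condition.

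Section 2.4 has all variables measured at the initial assessment, so a baseline CIPN20 score will exist. It also lists "Type of chemotherapy and number of cycles" among the personal and sociodemographic variables. Section 2.4.1 makes CIPN20, on a 0–100 scale, the primary outcome.

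Section 2.6 allocates without strata: "Those assigned an odd number were placed in the experimental group, while those assigned an even number were placed in the control group". Section 2.5 sizes the trial on a two-group t-test. For two independent groups, Section 2.8 names Student's t ("parametric test for independent samples") or the Mann–Whitney test. Its only multivariable model is a logistic regression for events that are not identified.

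**The concern.** Neuropathy caused by chemotherapy depends on what was given and how much of it. The criteria as listed can admit patients on different regimens and at different cycles, hence with different neuropathy scores at entry. The plan evidently expects this variation, since it records regimen and cycles, but neither allocation nor the named two-group tests use the information.

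Two things are at stake, and they should be kept apart:

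- **Precision.** Outcome variation that baseline score, regimen and cycles could explain is left in the residual, and a chance imbalance between two groups of 22 is carried into the estimate.
- **Dilution.** If some recruits receive a regimen that cannot cause neuropathy, they cannot benefit on the primary outcome, and the average effect shrinks with their share.

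**Working it through.** **Inputs from Section 2.5:** d = 1.11, significance level 0.05, power 95%, 38 evaluable (19 per arm), 44 recruited. Sidedness is not stated.

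**Assumed, not in the documents:** R², the share of outcome variance explained by the covariates; and f, the share of patients who cannot develop CIPN.

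**Step 1. Reproduce the plan's figure.** For n per arm, the t-test has noncentrality d × √(n/2) and 2n − 2 degrees of freedom. With n = 19: 1.11 × √9.5 = 3.42 on 36 df.

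- One-sided 0.05 (critical value 1.688): power 95.6%. The 38 is reproduced.
- Two-sided 0.05 (critical value 2.028): power 91.4%. For 95% power, 23 per arm (46 in all) would be needed.

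The gap between 95% and 91.4% therefore comes from sidedness and has nothing to do with eligibility. Both versions are carried forward where dilution is considered.

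**Step 2. What adjustment could recover.** With residual variance reduced by the factor 1 − R², the effective d is 1.11/√(1 − R²). Two-sided, 19 per arm:

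| R² (assumed) | Effective d | Power |
|---|---|---|
| 0 | 1.11 | 91.4% |
| 10% | 1.17 | 93.9% |
| 20% | 1.24 | 96.1% |
| 30% | 1.33 | 97.8% |

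Spending three degrees of freedom on three covariates (33 instead of 36) changes these powers by no more than about 0.1 percentage point. The table takes 1.11 as standardised by the unadjusted SD.

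**Step 3. What dilution would do, if present.** If f cannot develop CIPN, the SD is unchanged, and 1.11 describes a wholly at-risk population, the average effect is 1.11 × (1 − f). With 19 per arm:

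| f (assumed) | d | Power, one-sided | Power, two-sided |
|---|---|---|---|
| 0 | 1.11 | 95.6% | 91.4% |
| 10% | 1.00 | 91.6% | 85.0% |
| 20% | 0.89 | 85.1% | 75.9% |

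**Step 4. The two do not cancel.** A main-effect covariate for regimen lowers the residual variance but leaves the average treatment effect at 1.11 × (1 − f). Only the composition of the sample changes that effect.

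**The case against.** A reader might infer that patients who cannot develop CIPN are in the trial and that its power is therefore well below 95%. The documents do not support that. They give no regimen mix, so f may be close to zero. Recruitment is described as adjuvant, which narrows the population beyond what the criterion alone suggests. Section 2.5 takes d = 1.11 from earlier studies, one of them described as in the same group of patients. If their regimen mix was similar, any dilution is already in d, and applying 1 − f would count it twice. Starting the decline from 91.4% without comment would also charge eligibility with a loss that belongs to sidedness. These points stand, and they make dilution conditional.

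A second inference would be that mixed exposure biases the comparison. With random allocation it does not: it adds variance and leaves room for chance imbalance.

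It can also be said that Section 2.8 is a general menu which assigns no test to CIPN20, that it includes a repeated-measures F test and a regression open to relevant variables, and that covariates may be settled in an analysis plan not shown. This stands in part. But the logistic model does not analyse a 0–100 score, and both the sample-size test and the named two-group tests are unadjusted. The point is a better method than those stated, not a complaint that detail is missing. For the same reason, the article's silence on whether it aims at prevention or treatment of CIPN is not held against it.

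Finally, broad entry matches the stated objective, and most secondary outcomes need no neurotoxic regimen. That is fair, and it is why the eligibility change is secondary.

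**Conclusion.** The point holds as a loss of precision that can be avoided with data already planned. The tests named for comparing two groups leave baseline CIPN20, regimen and cycles in the error term, and unstratified allocation of 44 patients gives no protection against chance imbalance in them. The gain from adjustment is about 2.5 to 6.4 percentage points of two-sided power (91.4% to between 93.9% and 97.8%), on the assumption that the covariates explain 10% to 30% of outcome variance and that 38 patients are evaluable.

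The open eligibility criterion is a further weakness for a CIPN outcome, but its cost cannot be stated from the documents. It would be 4.0 points of one-sided or 6.4 points of two-sided power at f = 10%, and 10.5 or 15.5 points at f = 20%, only if d = 1.11 came from a wholly at-risk population. It could be nil.

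**What to change.** 1. **Primary analysis.** Specify an ANCOVA of post-intervention CIPN20 on group, with baseline CIPN20, chemotherapy type and cycles received at baseline as covariates fixed in advance. Define chemotherapy type in a few categories set by the investigators, for example neurotoxic or not, to suit a sample of this size. This needs no new data, provided the recorded cycle number is the number received at entry. It can be adopted at any time before the statistician sees outcomes by group.

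2. **Eligibility, only if enrolment is still open.** Restrict entry to patients receiving, or scheduled to receive, a regimen that the investigators define as neurotoxic. This is the only step that addresses dilution. Its cost may be slower recruitment. For patients enrolled under it, a neurotoxic yes/no covariate becomes nearly constant and adds little.

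Stratifying allocation by regimen is possible but not free: it would replace the odd/even scheme in Section 2.6, and the article describes recruitment and allocation in the past tense. The ANCOVA does not depend on it.
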